##### Collected data

The period of data collection for each participant is 3 weeks from the day of diagnosis. The first CRF that pops up comprises in- and exclusion criteria for participation in the study. If a resident is eligible to participate, a new CRF (T0) appears that includes resident characteristics (ie, sex and age), co-morbidities (eg, dementia, urinary tract abnormalities), and index consultation data such as signs and symptoms (specific, nonspecific and systemic), additional diagnostics (eg, urine analysis) and treatment (eg, whether antibiotics were started or not). The application automatically generates follow-up CRFs to be completed on day 3 (T1), 7 (T2) and 21 (T3). In addition to EHR-generated data, anonymous data on total antibiotic prescribing in the NH is collected in the 12 months before and during the study.

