##### Outcomes

The primary study outcome is appropriate antibiotic prescribing for suspected UTI at index consultation (yes/no), ie, prescribing in compliance with the treatment advice generated by the decision tool. Secondary study outcomes include the course of symptoms after the index consultation (ie, recovery, unchanged or deterioration), alternative diagnoses after assessment, changes in treatment policy (eg, start/stop antibiotics, adjustments in dose, type or duration) and motivation for these changes, complications, hospitalization, mortality and total antibiotic prescribing on the NH level.

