##### Analysis

The primary analysis assesses the difference between the intervention and the control group in appropriate antibiotic prescribing for suspected UTI, treated with antibiotics, at index consultation. A three level logistic regression model is used to account for variation at the NH/physician/resident level. lf there is no indication of random effects at the physician level, the three level logistic multilevel regression model is reduced to a two level model. Multilevel regression modeling is similarly used to compare secondary study outcomes between the two groups (linear or logistic, as appropriate). A second-order penalized quasi-likelihood estimation procedure is applied, using MLwiN software. Data on total antibiotic prescribing in the 12 months prior to the start of the study, and during the study period is explored descriptively in order to describe the potential impact of adjusted antibiotic prescribing for UTI on total antibiotic prescribing within intervention NHs, compared to control NHs.

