#### Data collection

Both in the intervention and the control group, physicians structurally report signs and symptoms of suspected UTI in electronic CRFs, for the study purposes. This may be considered an intervention in itself, as it provides insight into one’s treatment decision-making process, and additionally may promote behavior change due to the awareness of ‘being observed’ (ie, the Hawthorne effect) [22]. This would be in line with our previous study that showed a positive effect of data collection activities on the appropriateness of antibiotic prescribing decisions, which faded out over time [14]. In the current study we address this possible effect in the process evaluation (ie, the influence of study data registration is considered in interviews with physicians from both the intervention and control group) and by evaluating prescribing data (ie, a possible Hawthorne effect may be reflected by a change in antibiotic prescribing after study onset in both study groups, as compared with prescribing data prior to study onset).

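### Total antibiotic prescribing per home is a listed secondary outcome with a 12-month baseline, but it gets only a descriptive analysis and no baseline-adjusted comparison between arms

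*Protocol article*

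**What the plan says.** The Outcomes section of the protocol article closes its list of secondary outcomes with "complications, hospitalization, mortality and total antibiotic prescribing on the NH level". It does not mark the last of these as exploratory.

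Under Collected data, "anonymous data on total antibiotic prescribing in the NH is collected in the 12 months before and during the study". These data are separate from the case report forms completed for consenting residents with suspected UTI.

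The Analysis section then makes two statements. The general one is "Multilevel regression modeling is similarly used to compare secondary study outcomes between the two groups (linear or logistic, as appropriate"; no outcome is excepted. The specific one takes as its subject "Data on total antibiotic prescribing in the 12 months prior to the start of the study, and during the study period" and says that this material "is explored descriptively in order to describe the potential impact of adjusted antibiotic prescribing for UTI on total antibiotic prescribing", with intervention homes set against control homes.

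The pre-study data appear once more in the Discussion (Reflection on study design, Data collection). There a Hawthorne effect is to be looked for as a "change in antibiotic prescribing after study onset in both study groups, as compared with prescribing data prior to study onset".

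**The concern.** There are two problems. First, the general statement on secondary outcomes and the specific statement on this one do not agree as worded.

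Second, and more important, the plan states no interval, test or model for a between-arm contrast on this outcome. Homes differ in their prescribing for reasons unrelated to the trial. A described difference between two small groups of homes cannot be told apart from chance without a measure of uncertainty.

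This outcome also offers something that the others do not. The primary comparison is made in "appropriate antibiotic prescribing for suspected UTI, treated with antibiotics, at index consultation", a set formed after randomisation. The Sample size section expects 91% of control cases and 62% of intervention cases to be treated, so that set is expected to differ by arm. The case-based outcomes also depend on an unblinded physician entering a suspected UTI and on the resident's consent. As described, whole-home anonymous prescribing depends on none of these. It is therefore a useful supportive check on the trial's main message, and a description alone makes little use of it.

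**Working it through.** **The plan's own figures.** The Sample size section covers the primary outcome only: 66% v 86%, 80% power, 5% significance. With a two-sided test and pooled variance under the null:

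n = [1.96·√(2 × 0.76 × 0.24) + 0.842·√(0.66 × 0.34 + 0.86 × 0.14)]² / 0.20² = 70.4, so 71 per arm (stated: 72).

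The rest follows:
- 72/0.91 = 79 and 72/0.62 = 116 cases
- design effect 1 + 60 × 0.06 = 4.6
- 79 × 4.6 = 363 and 116 × 4.6 = 534, total 897
- 363/61 = 5.95 and 534/61 = 8.75, so 6 and 9 homes

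These figures reproduce. None of them sizes the total-prescribing outcome.

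**Inputs for that outcome.** Sixteen homes take part (Study design and setting). Their split by arm is not stated, so 6:10, 7:9 and 8:8 are used. The documents give neither the correlation r between a home's prior-year and study-period rates nor the between-home spread. Both are assumed and shown as ranges.

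**Gain from baseline adjustment.** The comparator is an unadjusted comparison of study-period rates. The large-sample variance ratio is 1 − r². With 16 homes, estimating the slope inflates this by an expected factor of 1 + 1/(16 − 4) = 13/12.

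| r (assumed) | 1 − r² | × 13/12 | Variance reduction |
|---|---|---|---|
| 0.5 | 0.75 | 0.81 | 19% |
| 0.7 | 0.51 | 0.55 | 45% |
| 0.8 | 0.36 | 0.39 | 61% |

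**What 16 homes could detect.** This uses noncentral-t power of 80% at two-sided 5%, with 14 degrees of freedom unadjusted and 13 adjusted. The standard error is SD × √[(1 − r²)(1/n₁ + 1/n₂)].

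| Analysis | Detectable difference, between-home SDs |
|---|---|
| Study period only | 1.51 to 1.56 |
| Adjusted, r = 0.5 | 1.31 to 1.36 |
| Adjusted, r = 0.7 | 1.08 to 1.12 |
| Adjusted, r = 0.8 | 0.91 to 0.94 |

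The adjusted rows omit the 13/12 factor, which would raise them by about 4% (√(13/12) = 1.04). For an assumed between-home coefficient of variation of 0.2 to 0.4, the relative differences are about 30% to 62% unadjusted and 22% to 45% at r = 0.7.

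**What effect might be expected.** The planned fall in prescribing per suspected UTI is (91 − 62)/91 = 32%. The Background says only that UTI takes the largest share of antibiotic prescribing. If that share is 30% to 50% (assumed), the fall in total prescribing is 0.32 × 0.30 = 10% to 0.32 × 0.50 = 16%. Even the most favourable combination shown (r = 0.8, coefficient of variation 0.2) detects 0.91 × 0.2 = 18% at best. Power would therefore be below 80% across these assumptions.

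**The case against.** The strongest reply has three parts.

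*The two statements need not conflict.* The general sentence suits resident-level outcomes nested in physicians and homes. If total prescribing is one value per home per period, a resident/physician/home model cannot apply, and the specific sentence reads naturally as an exception. This stands as far as it goes: the inconsistency is one of wording. It does not explain why a listed secondary outcome should have no measure of uncertainty.

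*Description is defensible.* The trial was not sized for this outcome, there are 16 homes, and all indications dilute a UTI effect. The decision tool also runs only for consenting residents (70% expected), which could dilute it further. This stands as a limit on what to expect. It argues for showing the imprecision in an interval and for calling the estimate supportive.

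*The gain is conditional.* The correlations are assumed, and the comparator is an unadjusted follow-up analysis that the plan does not propose. Both are true, so the percentages illustrate the value of adjustment and do not measure a loss against the planned analysis.

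A reader might also infer more than the documents support:
- That the baseline is never used. It is: the Analysis section describes the prior 12 months, and the Discussion uses them for the Hawthorne check.
- That this outcome is fully protected by randomisation. The protocol does not say so. Independence from the UTI label, consent and the treatment decision is inferred from how the data are collected.
- That the baseline rate belongs in the primary model. Nothing shows that prescribing volume predicts appropriateness, so this is not asked for.

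**Conclusion.** The point holds in a limited form. Total prescribing per home is a listed secondary outcome with a year of pre-study data. The plan gives it a description only and does not bring the baseline into any adjusted between-arm comparison. The trial will therefore be unable to say whether a difference between arms exceeds chance.

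Baseline adjustment would lower the variance by about 19%, 45% or 61% against an unadjusted follow-up comparison, for assumed correlations of 0.5, 0.7 or 0.8. It would not turn the outcome into a well-powered test: on the assumptions shown, the plausible effect of 10% to 16% is smaller than 16 homes could reliably detect. The benefit is an honest estimate with its uncertainty. The primary analysis and its sample size are untouched, so this is a modest, low-cost improvement. An analysis plan that is not shown may already add such a model; if so, the article's wording should be brought into line with it.

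**What to change.** In the Analysis section, replace the descriptive-only analysis with one home-level regression (16 rows): the log prescribing rate during the study on arm, adjusted for the same home's log rate in the prior 12 months, with inference from a t distribution on 16 − 3 = 13 degrees of freedom. Report the rate ratio with its 95% confidence interval, labelled as a supportive secondary estimate. The descriptive before/after display can stay beside it.

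Limit the multilevel-regression sentence to the other, resident-level secondary outcomes.

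State the denominator (resident-days or beds), and say whether the geriatric rehabilitation wards, which are excluded from the trial, are counted, with the same ward coverage in both periods.

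Cost: analysis wording, one small regression, one degree of freedom (13 instead of 14), and a denominator that the article does not say is collected. The prescribing data themselves are already planned. The interval will probably be wide, and the text should say so in advance.

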### Process evaluation

The process evaluation includes investigation of the quality of the intervention (decision tool, physician education and nursing staff education) and the implementation process, including barriers and facilitators that are involved. To this end, quantitative (cRCT data, questionnaires for NH professionals) and qualitative (semi-structured interviews with NH professionals) approaches are combined. Among professionals participating in the control group, we use similar resources to evaluate potential influences of participation in the current study or in other initiatives addressing appropriate prescribing, on antibiotic prescribing behavior.

Quantitative cRCT data is collected on several indicators for intervention quality, such as compliance with the treatment advice generated by the decision tool, and on motivations for deviation from the treatment advice. Questionnaires and semi-structured interviews are used to collect additional data on intervention quality, data on the implementation process, and data on barriers and facilitators for the implementation and use of the intervention. Regarding the latter, special attention is paid to the applicability of the decision tool in residents with limited abilities for self-report of symptoms, such as residents with dementia and residents with communicative disabilities (eg, stroke patients with aphasia). Questionnaires are distributed to all nursing staff and physicians of the participating locations. Interviews are held with a varied selection of these professionals (i.e. from very actively to poorly involved professionals). For the interviews we use a topic list based on the consolidated Framework for Implementation Research (cFIR) of Damschroder [18].

Univariate and multivariate analyses are performed to study associations between (non)adherence to the treatment advice and relevant resident characteristics (eg, dementia, incontinence, aphasia). ln addition, we investigate whether the level of implementation of the intervention is associated with adherence to the treatment advice. Finally, we describe facilitators and barriers that may explain differences in the use and implementation of the intervention. These facilitators and barriers are extracted from descriptive questionnaire analysis and from deductive thematic analysis of interviews.

## Discussion

This protocol paper described the design of a cRCT to evaluate whether an EHR-integrated decision tool in combination with education results in an increase in appropriate antibiotic prescribing for NH residents with suspected UTI. The decision tool under investigation was recently developed in an international Delphi procedure [4]. To the best of our knowledge, this is the first RCT to evaluate its use, and in addition, the first to evaluate the implementation of an electronic decision support for UTI in this setting. The studied intervention has the potential to improve diagnostic evaluation and treatment for suspected UTI in NH residents, and so contribute to the increasing antibiotic stewardship efforts in this setting.

### Reflection on study design

#### Informed consent procedure

The pre-emptive informed consent procedure applied in our study implies that all residents of participating NH wards are asked for informed consent, whereas only those who develop a suspected UTI during the study period become eligible for participation. This method allows physicians to use the decision tool and to start collecting data immediately after they consider a UTI. This would not be possible if physicians would have to ask for consent at the time of diagnosis, as legislation requires allowing time to reflect before deciding on study participation. The disadvantage of this pre-emptive informed consent procedure is that it is very time-consuming and puts a burden on residents, and/or their representatives, that will never become eligible to participate in our study.

#### Inclusion criteria

We aim to include participants that represent the general NH population and therefore apply broad inclusion criteria. Whereas people with dementia are often excluded from research [19], in our study it is especially important to include this group. Previous research showed that inappropriate antibiotic treatment for UTI is especially common in NH residents with dementia, as a consequence of communication issues and a high prevalence of nonspecific symptoms such as mental status change [3]. The vulnerability of this patient population emphasizes the importance of considering other causes for nonspecific signs and symptoms, and of introducing appropriate management. An important element of the process evaluation of the current study is to assess applicability of the decision tool in residents with dementia. If this would turn out to be limited, the results may provide clues for optimizing the decision tool for this specific population.

#### Intervention

In line with reports on computerized decision support systems for antibiotic prescribing in other health care settings, we believe that our intervention can be powerful in promoting appropriate antibiotic prescribing in the NH setting [20, 21]. The benefit of automatically generated treatment advice may be further reinforced by the fact that all physicians receive training on the content and background of the decision tool. Another strength of our intervention is its multidisciplinary character. The intervention is not solely oriented towards physicians, but also towards nursing staff. Nursing staff plays an important role in diagnosing UTI, as they observe and communicate signs and symptoms and may perform urine tests. In addition, they play an important role in communicating treatment decisions to residents and/or their family members. We therefore believe that involving nursing staff is a prerequisite for implementing changes regarding UTI diagnosis and management.

A potential pitfall is that access to a device with the EHR is needed at the time of treatment decision making in order to use the electronic decision support. If this is not the case, physicians may make treatment decisions before they received treatment advice. We anticipate this problem by providing pocket cards displaying the decision tool for these situations.

#### Data collection

Both in the intervention and the control group, physicians structurally report signs and symptoms of suspected UTI in electronic CRFs, for the study purposes. This may be considered an intervention in itself, as it provides insight into one’s treatment decision-making process, and additionally may promote behavior change due to the awareness of ‘being observed’ (ie, the Hawthorne effect) [22]. This would be in line with our previous study that showed a positive effect of data collection activities on the appropriateness of antibiotic prescribing decisions, which faded out over time [14]. In the current study we address this possible effect in the process evaluation (ie, the influence of study data registration is considered in interviews with physicians from both the intervention and control group) and by evaluating prescribing data (ie, a possible Hawthorne effect may be reflected by a change in antibiotic prescribing after study onset in both study groups, as compared with prescribing data prior to study onset).

### Reflection on study context

#### Revised guideline on UTI

We originally intended to evaluate the decision tool before its content would become usual care. However, during the final preparations of our study, the decision tool was incorporated in the revised guideline on UTI of the Dutch Association of Elderly Care Physicians (Verenso). From that moment on, the decision tool has been accessible for all physicians, including the physicians in our control group. Nonetheless, it is widely known that implementation of guidelines takes a substantial amount of time. In addition, earlier studies showed that 30 to 40% of the patients are not treated according to the current scientific evidence [23]. As the implementation of the decision tool represents a true paradigm shift (ie, the construct ‘UTI’ has been altered, which requires a different approach to nonspecific signs and symptoms and asks for changing habits with regard to urine testing) [4, 11], we anticipate that the implementation of this particular UTI guideline is even more challenging. The intervention that we evaluate in the current study may provide the support that is needed to provoke the much needed change in diagnosis and management of UTI.

#### External antibiotic stewardship efforts

Over the past few years there has been increased scientific and political attention for antibiotic stewardship in the long-term care setting in the Netherlands [24]. This has triggered a wide range of activities by several parties, focused on improving infection prevention and appropriate antibiotic use in NHs. The above mentioned UTI guideline revision is one of these activities. In the process evaluation, we establish if and to what extent the NHs in our study have participated in these activities. This is highly important for the interpretation of the current study results, as some activities might influence our primary study outcome: appropriate antibiotic prescribing for suspected UTI.

#### Decision tool not validated

Although the decision tool is incorporated into the aforementioned revised UTI guideline, it has not been validated to date. This implies that potential consequences of using the decision tool, in terms of disease course and resident safety, have not yet been investigated. Furthermore, after publication of the revised guideline, professionals raised several questions about the decision tool, in particular about its applicability to residents with dementia. Our study is of great importance to provide clarity in these issues.

This is the first cRCT to evaluate the recently developed, international decision tool for empiric treatment of suspected UTI in NH residents. Implementation of the decision tool includes integration into the EHR combined with multidisciplinary-oriented education on its content and use. Study findings will elucidate the effect of the intervention on appropriate antibiotic prescribing for suspected UTI, and provide insight into the applicability of the decision tool in NHs in general and in specific subgroups of NH residents, such as residents with dementia. With this study we aim to contribute to antibiotic stewardship efforts in the long-term care setting.

## Data Availability

The datasets generated and/or analyzed during the current study will be deposited in the repository PURE within a maximum of 3 months after publication of study results. The dataset(s) involved will be anonymised/pseudonymised and can be accessed under restrictions.

## Abbreviations

EHR: Electronic Health Record
NH: Nursing Home
cRCT: Cluster Randomized Controlled Trial
UTI: Urinary Tract Infection
